# Study Synopsis

| Title of clinical trial |  | Geriatrics and traumatology co-managing fragility fractures: effectiveness and success of implementation in a single centre setting |
| --- | --- | --- |
| Protocol Short Title/Acronym |  | G-COMAN FRACTURES |
| Sponsor name |  | UZ Leuven |
| Principal Investigator |  | [name] |
| Medical condition or disease under investigation |  | Older fragility fracture patients |
| Purpose of clinical trial |  | 1) To evaluate the effectiveness of a nurse-led geriatric-traumato co-management program using outcome indicators  2) To evaluate the feasibility of a nurse-led geriatric-traumato co-management program  2.1 To evaluate the reach and fidelity  2.2 To evaluate implementation targets 2.3 To evaluate implementation determinants  3)To evaluate the process of implementation of a nurse-led geriatric-traumato co-management program  3.1 To evaluate the reach and fidelity  3.2 To evaluate process outcomes |
| Primary objective |  | 1) Effectiveness evaluation: To determine if geriatric co-management is superior in preventing in-hospital complications |
| Secondary objective (s) |  | 1) Effectiveness evaluation: To determine if geriatric co-management is superior on following outcome indicators:  - length of stay  - unplanned readmissions within 30 and 90 days  - mortality  - functional status  - nutritional status  - quality of life  - falls and new fracture rate  - Discharge to a higher care level  - secondary fracture prevention started  - Cost-benefit of G-COMAN program  2) feasibility and process evaluation: To evaluate if geriatric co-management was successful implemented on the traumato ward:  -2.1 & 3.1: reach of the program and fidelity towards the core components of the care model  - 2.2: implementation targets  - 2.3: implementation determinants  -3.2: process outcomes:  * time to start physiotherapy  * time to start dietary advice  * use and duration of physical restraints  * use and duration of indwelling catheters (urinary tract catheter or intravenous catheter)  * Medication reconciliation at admission and discharge  * referral to geriatric day clinic  * referral to fracture liaison services |
| Trial Design |  | pre-post implementation study on the traumatology ward of the University Hospitals Leuven. |

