### 3.3 Secondary endpoints

1) Effectiveness evaluation

The secondary endpoints include comparison between the two groups on **patient outcome**:

- Length of hospital stay

- quality of life: EQ-5D^10^ (at admission, discharge, 1 month, 3 months, 6 months and 12 months post-surgery)

- functional status: Parker Mobility Score^11^, modified Barthel Index^12^, Lawton and Brody Scale^13^, Katz index (admission, discharge, 1 months, 3 months and 6 months post-surgery).

- hospital readmissions (30 and 90 days after discharge)

- falls (= “an unexpected event in which the patients comes to rest on the ground, floor or lower level”) and new fractures, either by retrospectively checking electronic patient record for any contact after discharge to any hospital or emergency department stating the occurrence of falls or new fractures) and by a questionnaire send out to patient and care givers. (admission, in-hospital, at discharge, at 1, 3, 6 months post-surgery 12 months post-surgery)

- Living situation: defined in 5 categories: living alone at home, living with spouse/partner, living with children, assisted living, living in a facility with 24h care such as nursing home). Details of care provided will be recorded as one of the following categories: 24h care, daily, irregular, no care. (admission, discharge, 1 month, 3 months post-surgery, 12 months after surgery)

- mortality (in-hospital, 1 month post-discharge and 12 months after discharge)

- secondary fracture prevention: documentation of fall risk assessment, medication review of calcium/vitamin D use and osteoporosis treatment, appointment to fracture liaison service (12 months after surgery)

- nutritional status: Mini Nutritional Assessment (MNA) ^14^ (at admission, 1 month, 3 months and 6 months post-surgery)

- cost-benefit analysis:

Costs will be assessed using a model that registers key hospital activities from the electronic patient record (KWS): 'beeldvorming', 'daghospitalisatie', 'dialyse', 'functiemeting', 'hospitalisatie', 'hospitalisatie ITE', 'labo', 'operatiekwartier', 'paramedische staf', 'raadpleging', 'raadpleging functiemeting', 'radiotherapie', 'spoedgevallen'. The model was developed by UHL.

2. Feasibility evaluation (is the intervention successfully implemented?):

2.1:

- the reach of the program (% of all eligible patients that were included in the G-COMAN program, defined as the patients who completed the questionnaire)

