### 3.4 Trial Design

single-centre pre-post implementation study on the traumatology ward of the University Hospitals Leuven

**Usual care (pre-cohort):** the control group receives usual care on the traumato ward. This means that the patient is cared for by a surgical resident. The interprofessional team furthermore consists of ward nurses, a physiotherapist, an occupational therapist and a social worker. No tailored geriatric protocols are available to the traumato team, except for those that are available hospital-wide for all patients (e.g. fall prevention, delirium). Geriatric expertise is available upon active request by the traumato team and includes the comprehensive evaluation of the patient by a geriatric nurse (consultation model).

Due to the design of the G-COMAN strategic project and its predefined strict timing schedule (a phased implementation with the need of a rapidly full implementation), the timeframe for inclusion of the pre-cohort is limited. At the end of the pre-cohort, the predefined sample size will not be reached. To obtain sufficient included patients in the pre-cohort, this patient cohort will be supplemented with patients of which retrospectively information will be gathered. This results in a pre-cohort that will be partly prospective and partly retrospective.

**Geriatric co-management intervention, quality-improvement project G-COMAN (post-cohort):** A dedicated traumato nurse (G-COMAN nurse) will systematically perform a frailty screening in all newly admitted older patients on the traumato ward to evaluate if they are to be included in the G-COMAN program. In eligible patients, a comprehensive geriatric assessment (CGA) will be performed by the G-COMAN nurse. Based on identified potential problems, a tailored care plan based on predefined geriatric protocols will be launched. As part of the project a geriatric specialist nurse will provide every weekday training and education of the G-COMAN nurse and other team members on the traumato ward. The implementation of automated care plans and predefined geriatric protocols will be coordinated by a G-COMAN project coordinator, as well as the organisation of focus groups and intervisions to ensure smooth and supported collaboration.

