### At discharge

The research assistant will monitor the incidence of complications using patient assessment (4AT) and by monitoring the patients record throughout hospitalization, and will assess the outcomes on hospital discharge using patient interview. **Discharge date, medication and mortality** will be evaluated based on the electronic patient record. **Functional status** is measured using the Parker Mobility Score^11^, Barthel Index ^12^, Katz index and Lawton and Brody scale based on reports, if possible from the patient, from next of kin or from nursing staff. **Quality of life** will be evaluated using the EQ-5D questionnaire. **Fall history** will be evaluated using a questionnaire. **Cognition** will be assessed using the Mini-cog test. **Living situation** will be defined within the next 5 categories: living alone at their own home, living with a spouse/partner at their own home, living with children or sibling, living in assisted living facility, living in a facility with 24u care (nursing home, rehabilitation setting,…). Details of care provided will be recorded as one of the following categories: 24h care, daily, irregular, no care. Variables that can be retrospectively collected are as follows: discharge date, medication, mortality, fall history and living situation.

Also **several process outcomes** of the G-COMAN program will be evaluated using registrations in the electronic patient records and by patient interviews: reach of the program (% of eligible patients that were effectively enrolled into the program), fidelity to the program (% of patients included in G-COMAN traumatology program who had a screening or assessment focusing on *delirium, nutritional status, pressure ulcer risk* using a validated tool within 48h of admission to traumatology ward) and specific care process; such as the *time to start physiotherapy*; *time to start dietary advice*; use, *type and duration of fixation;* *use, duration and reason of indwelling catheters (urinary tract catheter or intravenous catheter); medication reconciliation; referral to geriatric day clinic* for follow-up; *and referral to a fracture liaison service (Zoledronate infusion or metabolic bone consultation).*

*Cost-benefit will be calculated by UHL financial division using the UHL cost model based on retrospective data collected at least 3 months post-discharge.*

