### 3 months after discharge

Patients or their care givers will receive a letter by post with instructions and an assessment questionnaire for follow-up assessment at 3 months post discharge. If case of no response, the researchers will contact the patient / care giver by telephone to complete the assessment. The following items will be evaluated: **functional status** (Parker Mobility Score, Barthel Index, Lawton and Brody Scale, Katz index), **Quality of Life** (EQ-5D), **residential status**, **nutritional status**, **readmission** the **presence of new falls and fractures** as well as use of calcium/vitamin D and anti-osteoporosis **medication** in a questionnaire. Only readmission will be retrospectively collected.

Mean in-hospital costs will be calculated by UHL business manager using the UHL cost model .

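### The cost-benefit endpoint draws only on hospital activities registered in the patient record, does not show that programme resources are counted, and fixes no single cost window

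*Protocol*

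**What the plan says.** The Study Synopsis lists "Cost-benefit of G-COMAN program" among the secondary objectives.

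Protocol section 3.3 fixes the source of the costs: "Costs will be assessed using a model that registers key hospital activities from the electronic patient record (KWS". It names 13 categories from a model built by the hospital. They cover imaging, day hospital, dialysis, function tests, ward and *ITE* hospitalisation and laboratory, and the list ends with "operatiekwartier', 'paramedische staf', 'raadpleging', 'raadpleging functiemeting', 'radiotherapie', 'spoedgevallen". It says nothing about what each category contains, and it gives no time horizon.

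Section 3.4 describes what the programme adds to the ward:
- a nurse who screens and assesses patients: "A dedicated traumato nurse (G-COMAN nurse) will systematically perform a frailty screening in all newly admitted older patients";
- a trainer: "a geriatric specialist nurse will provide every weekday training and education of the G-COMAN nurse and other team members";
- a project coordinator who looks after care plans and protocols and organises focus groups and intervisions.

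The same section says that in usual care a geriatric nurse evaluates patients when the ward team asks for it.

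Section 5.1 speaks about cost timing twice. Under the discharge heading, the financial division calculates cost-benefit "based on retrospective data collected at least 3 months post-discharge". Under the three-month heading: "Mean in-hospital costs will be calculated by UHL business manager using the UHL cost model". The flowchart in section 3.6 has no row for costs.

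**The concern.** A cost-benefit result for a programme has to set the programme's own cost against what it saves. The model described here counts activities registered for individual patients. Teaching staff and coordinating protocols generate no such registration, so there is no evident route by which their cost reaches the result. If it does not, the analysis compares savings in bed days, tests and consultations with only part of the spending that produced them.

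The cost window matters for the same comparison. Readmissions up to 90 days, day-clinic visits and fracture liaison visits are all outcomes or processes that the programme is meant to change. Whether their cost counts depends on which statement in section 5.1 governs. Without one fixed window, the finance staff must choose, and they may choose differently for the retrospective and prospective patients.

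**Working it through.** The protocol states no unit cost, staffing level, mean cost or cost difference, so there is no figure to reproduce. The check sets the texts side by side and works out the direction of any error.

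**Step 1. Match programme resources to cost categories.**

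| Resource (section 3.4) | Tied to an individual patient? | Possible home in the section 3.3 list |
| --- | --- | --- |
| G-COMAN nurse: screening, assessment, care plan | Yes | Possibly *hospitalisatie* or *paramedische staf*; not stated |
| Geriatric specialist nurse: weekday training of staff | No | None evident |
| Project coordinator: protocols, focus groups, intervisions | No | None evident |
| Usual care: geriatric nurse consultation on request | Yes | Possibly *raadpleging* or *paramedische staf*; not stated |

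Section 6 (Assessment of efficacy) places the implementation in a separate hospital strategic project, outside this study. That fits with the programme's cost being held elsewhere, but does not prove it.

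**Step 2. Direction of the error.** For each cohort, let H be the mean cost per patient that the model captures, and u the mean cost of geriatric nursing and programme work that it does not capture.

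- Full difference: (H_post + u_post) − (H_pre + u_pre)
- Difference the plan would report: H_post − H_pre
- Reported minus full: −(u_post − u_pre)

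The reported difference is too low by u_post − u_pre. If usual-care consultation is fully captured, u_pre = 0 and the error equals the uncaptured programme cost per patient. If consultation is also uncaptured, the error shrinks by that amount. If everything is captured, the error is zero. Training and coordination belong to the programme only, so if they are uncaptured they enter u_post and not u_pre.

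**Step 3. Cost window.** The two statements in section 5.1, read with the list in section 3.3, allow at least three scopes:

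| Reading | What is counted | 90-day readmissions counted? |
| --- | --- | --- |
| A. Index stay only, data extracted no sooner than three months later | In-hospital costs of the first admission | No |
| B. All costs at this hospital up to three months | Index stay plus readmissions, emergency visits and consultations | Approximately yes |
| C. All costs at this hospital up to the extraction date | As B, with no upper limit | Yes, and later costs too |

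Section 3.3 does not choose between them, and its consultation, day-hospital and emergency categories can all arise after discharge. The two statements in section 5.1 also name different calculating parties (financial division and business manager).

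Under reading C with a single extraction date, follow-up would differ by cohort. Section 4.3 recruits the prospective pre-cohort from October 2021 to March 2022 and the post-cohort from September 2022 to September 2023. The last pre-cohort month precedes the first post-cohort month by 6 months, and the first precedes the last by 23 months. This holds only if both conditions apply, and the protocol states neither.

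**The case against.** The strongest reply is that the category names do not reveal what the model contains. The G-COMAN nurse is a ward nurse, so her cost could already sit in the hospitalisation category. This stands: a reader might infer from the list that all programme staffing is omitted, and the documents do not support that. The reply is weaker for training and coordination, because a model fed by registered patient activities has no evident place for them.

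Second, geriatric nursing input is not wholly new in the post-cohort, since usual care offers it on request. This also stands. The relevant quantity is the incremental cost; charging programme time to the post-cohort alone could tilt the result against G-COMAN.

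Third, the two timing statements can be read together: the first may give the earliest date for extracting the data, the second the costs to be calculated. A reader might infer a contradiction, or an open accrual period that loads more cost on earlier patients. Neither is established. What remains is an ambiguity about scope.

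Fourth, a reader might add that the cohorts fall in different years and that prices may differ. The protocol nowhere says that nominal prices will be used, price year is normally settled in a costing or analysis plan, and rising prices would make the later cohort look dearer, which works against G-COMAN. This forms no part of the point.

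Finally, costing from the hospital's perspective is a legitimate choice for a hospital-run programme and is not criticised here.

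**Conclusion.** The point holds in conditional form. As written, the costing would probably leave out part of the programme's own cost, at least the training and coordination. Whatever net amount is left out understates the post-minus-pre cost difference by the same amount per patient, in favour of G-COMAN. This rests on the assumption that a model of registered patient activities carries no charge for work that is not tied to patients; the protocol neither confirms nor denies this.

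A reader might go further and call the endpoint biased towards the programme. The documents do not support that without the condition: some staff cost may be captured, and the unclear window has no determinable direction unless one particular reading is adopted. The size cannot be estimated, nor can it be said whether it would change the conclusion.

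The cost scope is ambiguous and needs one definition. The consequence is confined to a secondary endpoint; the primary comparison of complications and the sample size are untouched.

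**What to change.** 1. In section 3.3, add a programme-cost line for the post-cohort: time of the G-COMAN nurse, the geriatric specialist nurse and the coordinator, divided by the number of patients the programme served. First ask the finance division what *hospitalisatie* and *paramedische staf* already include, so that nothing is counted twice. Cost the pre-cohort's geriatric consultation time on the same basis, so that the line is incremental.
2. Reconcile the two cost statements in section 5.1 (discharge and three months) and state one closed window in section 3.3, identical for the prospective pre-, retrospective pre- and post-cohorts. One example is from index admission to 90 days after discharge, for costs at this hospital; this matches the 90-day readmission endpoint.

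The cost is a protocol wording change and a limited request to the finance division for staff time and category contents. The downside is that the programme's cost result may become less favourable.

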Combining the successful results of G-COACH and the orthogeriatric care model abroad, we set up a care strategic project (2021-2024) for geriatric-surgical co-management within the University Hospitals Leuven, named **G-COMAN**. G-COMAN aims to optimize geriatric care in elderly surgical patients through a phased implementation of geriatric surgical co-management on the services traumatology, abdominal surgery and vascular surgery. This year (2021) is dedicated to pre-implementation. From 2022 onwards, G-COMAN will start implementing the program on the traumatology ward. Dedicated nurses will perform comprehensive geriatric assessments (CGA) in all patients aged 75 and older on the traumatology ward. By systematically organizing proactive care with collaboration and shared decision making between geriatric and surgical departments, postoperative care outcomes will hopefully improve.

This observational study will evaluate the **effectiveness of geriatric-traumatology** part of the G-COMAN program and will examine **which factors contribute to** a (non)successful **implementation** of the program as we aim to sustainable embed geriatric care aspects in the standard care of surgical services.

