- the fidelity towards the core components of the program (% of included patients who received the core components of the intervention). The core components are 1) the screening questionnaire, 2) comprehensive geriatric evaluation, 3) individual care plan and 4) follow-up.

- The fidelity towards the other intervention components:

- Patient received physiotherapy within 24h postoperative
- The patient was evaluated using the food quadrant method by a logistics employee
- Patient received swallowing screening by a nurse
- If there is no indication for an indwelling catheter, the patient is free of an indwelling catheter
- If a post-void residual volume of ≥ 300 ml is observed in a patient, the residual volume is removed using intermittent catheterization before end of shift after detection of symptoms
- If the urinary catheter was removed, the post-void residual volume is monitored using a bladder scan in the next shift
- If a patient has not passed stool for 3 days, the patient is prescribed oral laxatives before day 4 without stool
- If a patient has not passed stool for 5 days, the patient receives an enema before day 6 without stool
- If there is no indication for a physical restraint, the patients is free of a physical restraint
- If a patient is delirious, the DOS scale was followed up during the next shift
- If a patient reports a pain score of 4 or higher (out of 10), pain medication is given unless refused by the patient within 1h of onset of symptoms
- If a patient reports a pain score of 4 or higher (out of 10), the pain is re-evaluated within 1h of onset of symptoms
- If a patient did not take calcium/vitamin D supplements or anti-osteoporotic medication at admission, it was prescribed at discharge
- The patient was referred to a fracture liaison service

2.2: Implementation targets: awareness, knowledge, motivation to change, perceived acceptability and feasibility, and believe in the benefit, value and success of the program

2.3: Implementation determinants: facilitators and barriers of the program

3. Process evaluation (how well was the process of care changed?)

3.1: reach and fidelity will be reevaluated the same way as expressed above.

3.2: process outcomes

- time to start physiotherapy (as first day after surgery with a first registered contact in electronic patient record)

- % of patients receiving dietary advice and time to start dietary advice

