In between pre-cohort and post-cohort, a single intervention group will be recruited as part of a feasibility study, in order to evaluate if the intervention is implemented successfully. If this is not the case, the implementation will be adapted and revaluation of successful implementation will be planned.

Due to the nature of the study design, health professionals and patients cannot be blinded. Blinding of outcome assessors is not considered feasible due to limited resources.

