### Feasibility study

Before start of recruitment of the post-cohort, a feasibility evaluation in a single intervention group will be performed in order to be sure if the implementation of the intervention is delivered as intended. The feasibility of the intervention will be evaluated using a mixed-methods approach. First, the reach and fidelity (2.1) will be determined with a quantitative evaluation using the electronic patient record. The reach reflects the percentage of eligible patients that was included in the G-COMAN program. Inclusion in the program is defined as having received the questionnaire and a CGA. The number of patients who were actually included will be compared with the total number of eligible patients. The fidelity determines how well the intervention is implemented as defined by the protocol and reflects the percentages of included patients who received the core components of the intervention. Both the core components as the timing will be evaluated. The same baseline characteristics will be collected as in the pre- and post-cohort (variables at admission). Second, a survey will be sent out to all health care professionals working on the traumatology ward measuring the implementation targets (awareness, knowledge, motivation to change, perceived acceptability and feasibility, and believe in the benefit, value and success of the program) (2.2). The survey will consist of questions with each 5 response options: completely agree, agree, neutral, do not agree and completely do not agree (**appendix 3**). Thirdly, focus groups/interviews with all health care professionals will be organised to qualify the implementation barriers, namely the barriers and facilitators of the G-COMAN program (2.3). The expectations and experiences of the multidisciplinary traumatology team will be captured in a focus group/interview before start of the implementation, during the implementation and at the end of the implementation. An interview guide will be drafted to be used during the focus group. One researcher was the moderator and the second researcher observed the discussion and took notes. All interviews will be tape recorded and written out verbatim. Afterwards, the tape records will be deleted.

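### Inclusion in G-COMAN and fidelity are each defined in two ways, and one inclusion rule fixes fidelity on receipt of the geriatric assessment at 100%

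*Protocol*

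**What the plan says.** **Inclusion and reach.** Protocol section 3.3, item 2.1, expresses reach as the share of eligible patients "included in the G-COMAN program, defined as the patients who completed the questionnaire". The Feasibility study part of section 5.1 describes the same item 2.1, but there "Inclusion in the program is defined as having received the questionnaire and a CGA". The discharge part of section 5.1 has a third wording, "reach of the program (% of eligible patients that were effectively enrolled into the program", and does not say what counts as effective enrolment.

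**Fidelity.** Section 3.3 takes the share of included patients who received the core components: "The core components are 1) the screening questionnaire, 2) comprehensive geriatric evaluation, 3) individual care plan and 4) follow-up". The feasibility part of 5.1 and the process-outcome table in 3.6 also refer to core components. The discharge part of 5.1 instead defines fidelity as screening or assessment for delirium, nutrition and pressure-ulcer risk, "using a validated tool within 48h of admission to traumatology ward". Yet section 3.3, item 3.1, says the process evaluation measures reach and fidelity in the same way as the feasibility evaluation.

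**Who is due a CGA.** Background and rationale says "Dedicated nurses will perform comprehensive geriatric assessments (CGA) in all patients aged 75 and older on the traumatology ward". Section 3.4 describes a frailty screen of newly admitted older patients "to evaluate if they are to be included in the G-COMAN program", followed by a CGA in those found eligible.

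**Use of the result.** Section 3.4 says of successful implementation: "If this is not the case, the implementation will be adapted and revaluation of successful implementation will be planned". It gives no numerical limit.

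**The concern.** Reach and fidelity are named secondary endpoints. They are used in the feasibility evaluation before the post-cohort and again in the process evaluation. Because included patients form the numerator of one measure and the denominator of the other, two inclusion rules change both figures at once, in opposite directions.

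The rule that requires a CGA for inclusion also makes one fidelity component empty. The CGA is core component 2, so the share of included patients who received it can only be 100%.

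The two fidelity definitions do not measure the same thing. Pressure-ulcer risk appears neither among the four core components nor among the other intervention components listed in 3.3. An analyst could follow either section and claim to follow the protocol, and the choice could be made after the data are seen.

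**Working it through.** The protocol gives no counts or target values for reach or fidelity, so there is no stated figure to reproduce. The check is set arithmetic on the definitions.

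**Inputs**
- E: eligible patients (denominator of reach in 3.3 and 5.1).
- Q: those with the questionnaire. Section 3.3 says completed and 5.1 says received; I treat these as the same.
- C: those with the questionnaire and a CGA, so C ≤ Q.

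**Formulas**

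| Measure | 3.3 rule (questionnaire) | 5.1 rule (questionnaire and CGA) |
|---|---|---|
| Reach | Q/E | C/E |
| Fidelity, questionnaire | Q/Q = 100% | C/C = 100% |
| Fidelity, CGA receipt | C/Q | C/C = 100% |

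**Illustrative counts (assumptions, not from the protocol)**

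| E, Q, C | Reach, 3.3 | CGA fidelity, 3.3 | Reach, 5.1 | CGA fidelity, 5.1 |
|---|---|---|---|---|
| 100, 90, 70 | 90/100 = 90% | 70/90 = 78% | 70/100 = 70% | 70/70 = 100% |
| 20, 15, 9 | 15/20 = 75% | 9/15 = 60% | 9/20 = 45% | 9/9 = 100% |
| 15, 14, 7 | 14/15 = 93.3% | 7/14 = 50% | 7/15 = 46.7% | 7/7 = 100% |

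Whenever C < Q, the 5.1 rule lowers reach and raises CGA fidelity to 100%. The product of the two is C/E under both rules: (Q/E)(C/Q) = C/E and (C/E)(1) = C/E. The shortfall is therefore moved from one measure to the other, not lost.

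**Other components.** Care plan and follow-up remain informative under both rules, but their denominator changes. With E = 100, Q = 95, C = 60 and 55 patients receiving all four components, full receipt is 55/95 = 57.9% under 3.3 and 55/60 = 91.7% under 5.1.

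**Second fidelity definition.** Sections 3.3 and 5.1 (Feasibility study) count core components; 5.1 (At discharge) counts three types of screening within 48 hours. A patient can satisfy either without the other. Item 3.1 of section 3.3 requires the same measurement in both evaluations, so the discharge definition cannot stand beside it.

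**The case against.** The strongest reply is that both figures will be reported, so moving missed CGAs from fidelity to reach relabels one shortfall and hides nothing. The product identity supports this for a reader who sees both figures and knows which rule was used. It does not excuse two rules for one endpoint, nor a component that cannot fall below 100%.

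Three stronger readings are tempting, and the protocol does not support them.

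- **A reader might infer that the feasibility check could give opposite answers.** No success threshold is stated. The evaluation also uses a staff survey and focus groups or interviews, and fidelity there covers timing as well as receipt. No stated decision flips. The 48-hour definition sits with the discharge process outcomes, so that conflict mainly concerns the process evaluation.
- **A reader might infer that, with 15 feasibility patients, the definitional shift swamps sampling error.** It does not. For 12/15 the exact 95% interval is 51.9% to 95.7%, about 44 points wide, against a shift of about 20 points in the first example. Section 8.1 describes the 15 as patients receiving the intervention, so they are not the denominator of reach.
- **A reader might infer that the post-cohort will be frailer than the pre-cohort.** Sections 4.1 and 4.2 set no frailty criterion for either cohort. The screen in 3.4 governs entry to the programme, not to the study. The 3.6 table reports reach in the post-cohort, which is informative only if that cohort can contain patients outside the programme.

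One objection limits the remedy. If the frailty screen decides who is due a CGA, dividing CGAs by everyone with a questionnaire counts correctly handled screen-negative patients as failures. The 78% in the example would then not necessarily be a shortfall. This stands, and the denominator must allow for it.

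**Conclusion.** The point holds as an internal inconsistency in descriptive secondary endpoints. Inclusion has two incompatible definitions for item 2.1, and fidelity has two for measures that 3.3 says are taken alike. Under the 5.1 inclusion rule, fidelity on CGA receipt is 100% whatever happens on the ward.

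The size depends on how many patients with a questionnaire have no CGA. It is zero if C = Q. In the three sets of counts tabulated above, reach moves by 20 to about 47 points and CGA fidelity by 22 to 50 points. Those counts are assumptions.

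The 100% applies to CGA receipt only; care plan, follow-up and timing stay informative. Questionnaire fidelity is 100% under either rule, so it carries no information beyond reach. The primary endpoint, the sample size of 108 per group and the effectiveness comparison are not affected.

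**What to change.** Use one set of definitions in section 3.3, the process-outcome table in 3.6, and the discharge and feasibility parts of 5.1.

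1. **Reach:** questionnaire completed, divided by all patients meeting 4.1 and 4.2. Remove the CGA from the inclusion rule and replace the undefined reference to effective enrolment.
2. **Fidelity:** report CGA, care plan and follow-up separately, each among reached patients for whom that component is due under the programme. Report questionnaire receipt as reach only.
3. **Who is due a CGA:** reconcile Background and rationale (all patients aged 75 and older) with 3.4 (those selected by the screen). The programme team must settle this; the fidelity denominator then follows.
4. **48-hour screening:** report it as a separate process item, not as fidelity.

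The cost is protocol wording only. Reported CGA fidelity may fall below 100%, which is what makes it informative.
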